### Objectives

Our primary aim is to assess the potential preventive effects of antimalarials in reducing the incidence of moderate-to-severe forms of COVID-19 in patients with rheumatic diseases. Secondarily, we aim to determine the frequency of SARS-CoV-2 infection in patients with rheumatic diseases who are chronic users of antimalarials. For both objectives, patients with rheumatic diseases will be compared with members of their household who are not taking antimalarials.

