### Control Group

The control group will consist of healthy individuals aged >18 years, who are household cohabitants or work colleagues of patients with rheumatic diseases in the intervention group.

Contact with a suspected or confirmed case of COVID-19 is defined as an individual sharing accommodations with a patient with a rheumatic disease (eg, residing in the same house or environment as roommates, occupational colleagues, etc). The exposure grade assessment is individualized, considering the type of environment and the exposure time.

For each case, two household and/or professional contact individuals will be selected as controls. The choice of the first control is prioritized by flu-like symptoms and defined as the “symptomatic group,” including suspected or confirmed cases. Those without symptoms will comprise the “asymptomatic group;” both household and/or contact individuals can be selected, preferably paired for age and sex.

The household and/or workplace contacts were chosen to characterize the control group because of their high epidemiological value during community viral transmissions worldwide, instead of including nonusers of antimalarials with rheumatic diseases. Moreover, lupus patients without antimalarial treatment are quite uncommon, except in those with previous toxicity (maculopathy, allergy, long-term remission, etc).

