### Data Collection

Data are being collected regarding social, epidemiological, and demographic characteristics, as well as detailed information on antimalarials (type of salt, dosage, frequency, adherence during the pandemic) and rheumatic disease (diagnosis, disease activity). In addition, aspects related to comorbidities, smoking, alcohol intake, and concomitant medications are being recorded, as well as specific information about COVID-19 symptoms and main outcomes (hospitalization, need for intensive care unit, and death) in both groups (Multimedia Appendix 1).

All phone interviews are being conducted by health care professionals (eg, volunteer medical students), all previously trained by the principal investigator or subinvestigator from each rheumatology center (Figure 1). This training included a tutorial in PDF and video formats about each step of the study protocol. In addition, several WhatsApp-based groups were formed and supervised by the principal investigator, subinvestigator, or study coordinators to find the best solution for minimizing eventual problems.

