### Outcomes

Primary outcomes (at baseline and during the 24-week study period) are as follows:

SARS-CoV-2 infection (illness): suspected, suggestive, or confirmedDeathHospitalizationNeed for intensive care unitNeed for mechanical ventilationTotal hospitalization timeDate of occurrence of an adverse event (eg, death, hospitalization)

Secondary outcomes are as follows:

General clinical differences in COVID-19 course severity between rheumatic patients and nonrheumatic controls;Initial clinical differences and progression to moderate or severe course of disease between the two groups.

Confounding and adjustment variables are age, sex, comorbidities, concomitant medications, and flu vaccine.

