### Statistical Analysis

The data will be analyzed using descriptive statistics—absolute and relative frequencies for categorical variables and quantitative measures (mean, quartiles, minimum, maximum, and standard deviation) for numerical variables. The normality of the data will be verified using the Kolmogorov-Smirnov test.

A chi-square test will be used to assess the association between categorical variables with standardized adjusted residual calculation; Fisher exact test will be used for small samples. The linear associations between two variables of a numerical nature will be evaluated using Pearson correlation.

To evaluate the behavior of clinical variables between two points in time by group, analysis of variance (ANOVA) will be used, with repeated measures. In the case of nonnormality of data, the means of the groups at each time point will be compared using the Kruskal-Wallis nonparametric test. To compare the means between phone visits in each group, the Wilcoxon nonparametric test will be used.

The comparison between the means of numerical variables with normal distribution will be verified through the Student *t* test. If the assumption of normality is violated, the Mann-Whitney nonparametric test will be used.

Adjusted multiple linear regression models will be used to assess the simultaneous effects of sex, age, duration of illness, comorbidities, concomitant medications, and other confounding variables, according to group and predefined outcomes. For dichotomous dependent variables, a logistic regression model will be preferred. Survival analysis models, including log rank and Kaplan-Meier tests, adjusted for confounding variables, will be developed to assess the main outcomes over time. The time defined as the end date will be the date of a major event, such as illness with confirmation or suspicion of infection, hospitalization, or death.

Correlation analysis will be performed using the Pearson test to assess the relationship between the incidence rate of confirmed COVID-19 cases per 100,000 inhabitants and the proportion of symptomatic patients and controls in municipalities. Data of confirmed cases per municipality are available through the Brasil.io project [51]. The QGIGS Desktop 3.6.0 (Open Source Geospatial Foundation) will be used for map plotting.

SPSS, version 20 (IMB Corp) will be used in all analyses, and a *P* value <.05 will be considered significant.

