## Discussion

This study’s novel design, with its large sample of chronic antimalarial users, will enable us to perform a thorough prospective assessment (every 2 weeks) to explore whether vulnerability to SARS-CoV-2 infection may be associated with IMRD or to hydroxychloroquine after adjustments for cofounders, especially those related to other immunosuppressive drugs and comorbidities. On the other hand, it has some limitations, such as compliance and adherence; a potential shortage of HCQ (hydroxychloroquine) in some parts of our country; possible biases associated with recalling symptoms; inability to answer the phone (due to hospitalization or death), and lack of confirmatory tests (PCR tests for SARS-CoV-2 or antibody-based RNA [ribonucleic acid]) for all enrolled patients and controls, especially in those with nonsevere forms. Future randomized controlled trials may provide a better understanding of these differences.

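### Every patient has both the drug and a rheumatic condition and controls have neither, so the two-group models estimate a combined contrast, not the antimalarial effect named as the primary aim

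*Protocol article*

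**What the plan says.** The Objectives section of the protocol article states the effect sought: "Our primary aim is to assess the potential preventive effects of antimalarials". The outcome it names is the occurrence of moderate-to-severe COVID-19 among rheumatic patients. For both objectives it names the comparison: "patients with rheumatic diseases will be compared with members of their household who are not taking antimalarials". The Control Group section widens the controls to work colleagues, requires them to be healthy, and explains that rheumatic patients not on antimalarials were deliberately not used, partly because untreated lupus is uncommon.

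The Statistical Analysis section plans regression models for the "simultaneous effects of sex, age, duration of illness, comorbidities, concomitant medications, and other confounding variables, according to group" and the outcomes. The Outcomes section gives a different list: "Confounding and adjustment variables are age, sex, comorbidities, concomitant medications, and flu vaccine". *Duration of illness* is in the first list and not in the second, and it is not defined.

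The Discussion says that the design will allow the investigators to "explore whether vulnerability to SARS-CoV-2 infection may be associated with IMRD or to hydroxychloroquine after adjustments for cofounders", especially other immunosuppressive drugs and comorbidities. Its limitations cover adherence, drug shortage, recall, failure to reach participants and incomplete testing. Confounding by the rheumatic disease itself is not among them.

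**The concern.** Membership of the patient group carries two things at once: the drug, and a rheumatic condition together with whatever else comes with it (other treatment, contact with health services, behaviour during the pandemic). The primary aim attributes the between-group difference to the first alone. If the two cannot be separated in the data, a lower rate of moderate-to-severe COVID-19 in patients could be reported as drug protection when the drug does nothing. A real benefit could equally be hidden by a higher risk from the disease. The primary conclusion is at stake, not only its precision.

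The covariate *duration of illness* adds a second difficulty, because on neither plausible reading does it belong in a model that compares patients with controls.

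**Working it through.** The plan states no figure for the drug effect, so there is none to reproduce. The sample-size figure does not bear on this point. The question is what the planned models can identify.

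**Inputs (protocol article)**
- Patients: drug = 1 for all, since at least 30 days of use is an inclusion criterion. Rheumatic condition = 1 for all: IMRD, osteoarthritis or chikungunya-related arthropathy (Abstract, Methods; Inclusion Criteria).
- Controls: drug = 0 and rheumatic condition = 0 (Abstract, Objective; Objectives; Control Group).
- Enrolment (Results): 10,443 in total, of whom 5,166 are patients, leaving 10,443 − 5,166 = 5,277 others, taken here as controls.

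**Step 1: the cells**

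| | Drug | No drug |
|---|---|---|
| Rheumatic condition | 5,166 | 0 |
| None | 0 | 5,277 |

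Two of the four cells are empty by design.

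**Step 2: the model.** Write logit(p) = a + b·Drug + d·Disease + c·X, where X is any set of covariates. Drug = Disease = Group for everyone, so this becomes logit(p) = a + (b + d)·Group + c·X. Only b + d can be estimated, so the group odds ratio is OR(drug) × OR(disease).

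**Step 3: rank check.** A design matrix was built with the enrolment above and simulated covariate values.
- Intercept, drug, disease, age, sex, comorbidity: 6 columns, rank 5.
- The same plus duration, set to 0 in controls: 7 columns, rank 6.

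The missing rank is the drug/disease pair. Adding a covariate does not restore it.

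**Step 4: what one result would be compatible with.** Component values are assumptions. A group odds ratio of 0.70 arises from:
- drug 0.70 × disease 1.0 = 0.70
- drug 0.50 × disease 1.4 = 0.70
- drug 0.35 × disease 2.0 = 0.70
- drug 1.0 × disease 0.70 = 0.70
- drug 1.4 × disease 0.50 = 0.70

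So even the direction of the drug effect is not fixed by the group contrast.

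**Step 5: the non-IMRD subgroups.** Osteoarthritis and chikungunya patients have drug = 1 and IMRD = 0. With an assumed 5% share of patients, a model with intercept, drug, IMRD and age has 4 columns and rank 4. Drug and IMRD are then formally separable. The drug coefficient in that model, however, compares treated osteoarthritis and chikungunya patients with healthy contacts. It equals the drug effect only if those conditions carry no effect of their own. Adding a column for any rheumatic condition gives 5 columns and rank 4: the same aliasing returns.

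**Step 6: *duration of illness*.**
- Read as rheumatic-disease duration, it does not exist in controls. If it is left missing, a complete-case model drops every control and the group effect cannot be estimated (intercept, group, duration, age: 4 columns, rank 3). If it is coded 0, the model runs (variance inflation for group about 2 under a simulated duration distribution), but the group coefficient becomes a contrast at duration zero.
- Read as duration of the infection, a sense in which the Outcomes and Statistical Analysis sections also use the word illness, it is a consequence of the outcome and should not be adjusted for.

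**The case against.** **Drug and IMRD are not perfectly aliased.** A reader might infer that no regression could ever separate the two things the Discussion names. The documents do not support that, because the osteoarthritis and chikungunya subgroups use the drug without IMRD (Step 5). This stands. But no contrast using them is stated, and it would rest on patients whose own condition is again inseparable from the drug.

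**The design is disclosed and the language is cautious.** The Objectives name the comparator, the Control Group section justifies it, and the Discussion speaks of exploring an association and looks to future randomised trials. This stands as mitigation. It does not change the primary aim, which is worded as a drug effect, or supply the missing limitation.

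**The duration term may be harmless.** It is undefined, and the phrase *according to group* could mean models fitted within each group, where disease duration among patients is legitimate. This stands: a failed model is not demonstrated. What is shown is that the term has no sound use between groups, and the text does not exclude that use.

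**The adjustment set may be fuller than it looks.** A reader might infer that smoking and exposure grade are recorded for both groups and then ignored. The documents do not support that. Smoking is collected (Data Collection). Exposure grade appears only in the Control Group section: "The exposure grade assessment is individualized, considering the type of environment and the exposure time". No section says that it is recorded for both groups. The covariate list in Statistical Analysis is also open-ended, and the complete list may sit in a plan not shown.

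**Immunosuppressants are adjusted for.** Concomitant medications are in both lists and vary among patients, so part of the treatment effect can be modelled. This stands, and it is one reason not to read the illustrative products as estimates of bias.

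**Conclusion.** The point holds in this form. Antimalarial use and having any rheumatic condition coincide completely by design, so the planned patient-versus-contact models estimate one combined contrast. They cannot estimate the antimalarial effect set as the primary aim, and as planned they cannot tell IMRD from hydroxychloroquine after adjustment. This rests on the eligibility and control definitions alone, and no assumed number is needed.

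The size of any distortion cannot be derived from the documents. The odds ratios in Step 4 are illustrative assumptions, as are the 5% subgroup share and the simulated duration values.

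It may be tempting to conclude that a within-patient analysis would settle the drug question, since the study collects "detailed information on antimalarials (type of salt, dosage, frequency, adherence during the pandemic"). It would not. Dose and interruption may follow disease activity, toxicity or illness, and the Discussion itself lists adherence and supply as limitations. That no such analysis appears in the article is not counted as a fault here.

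**What to change.** 1. Restate the primary estimand and conclusion as antimalarial-treated rheumatic patients versus their household or work contacts. Withdraw the claim to attribute the difference to IMRD or to hydroxychloroquine, and add confounding by disease and its treatment to the limitations in the Discussion.
2. Define *duration of illness*, keep it out of every between-group model, and use it only in models within patients. Bring the covariate lists in Outcomes and Statistical Analysis into agreement.
3. Optionally, add smoking, contact type (household or work) and, if it is recorded for both groups, exposure grade to the adjustment set.
4. Optionally, report a within-patient analysis by dose and adherence, adjusted for diagnosis, disease activity and immunosuppressants. Label it supportive and itself confounded.

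Items 1 and 2 are changes of wording and model specification. They need no new data and are still possible, since the Results section says that analysis had not begun. The cost is a weaker headline claim. The within-patient analysis would use data already being collected but would have fewer events.

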**Figure 3 figure3:**
[figure not shown]
Suspected vs confirmed cases of COVID-19. RT-PCR: real-time polymerase chain reaction, IgM: immunoglobulin M, IgA: immunoglobulin A, IgG: immunoglobulin G, ELISA: enzyme-linked immunosorbent assay, IC: ion channel, ECLIA: electrochemiluminescence immunoassay.

Moderate-to-severe cases are defined as those that require hospitalization, mechanical ventilation, or result in death. Through direct contact with hospitals, hospitalized patients are being clinically evaluated in terms of longitudinal follow-up and treatment outcome, infection severity, length of stay, need for intensive care, mechanical ventilation, and cause of death.

Considering the heterogeneous community viral transmission in Brazil, some epidemiological approaches were developed to assure a similar path involving patients with rheumatic diseases and controls, such as the same pandemic COVID-19 curve in each city and region [41]. Therefore, after initial contact (V1), two strategies were adopted to maintain the follow-up of patients and to optimize the capture of main outcomes. Firstly, an active strategy is addressed in cases of flu-like syndrome and symptoms suggestive of COVID-19. For this strategy, the patient or household member is shown how to provide clinical data on the patient or his/her control through a toll-free telephone number (the 0800 system). Secondly, the patient is contacted every week by the REDCap team to gather relevant data on infection. An additional visit is conducted if the patient or control provides information about flu symptoms or disease activity via an unscheduled phone call or contact through the toll-free number. In both cases the individual will be advised to stay home and use painkillers or an antipyretic. In case of worsening/severe symptoms (eg, persistent cough or fever and shortness of breath), they will be advised to visit a hospital or to make an appointment with a physician involved in our study.

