## Results

This study is in the data collection phase. Study recruitment opened in March 2020. In an 8-week period (from March 29 to May 17), a total of 10,443 individuals enrolled at baseline (including 5166 patients with rheumatic diseases) from 23 tertiary rheumatology centers in 97 Brazilian cities. Data analysis is scheduled to start after all relevant data have been collected.

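### The municipality-level Pearson correlation ignores the binomial noise in each city's symptom proportion, so a non-zero r is pulled toward zero and, if city sizes are unequal, power is lost (ancillary analysis, minor priority)

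*Protocol article*

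**What the plan says.** Statistical Analysis names the method, "Correlation analysis will be performed using the Pearson test", and what it is to assess: "the relationship between the incidence rate of confirmed COVID-19 cases per 100,000 inhabitants and the proportion of symptomatic patients and controls in municipalities". The unit of analysis is therefore the municipality, with one observed proportion each. No weights, minimum number of participants or binomial model are mentioned. The section applies one threshold to all its analyses: a P "value <.05 will be considered significant". For dichotomous dependent variables, the same section prefers logistic regression.

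Results gives the scale: "a total of 10,443 individuals enrolled at baseline (including 5166 patients with rheumatic diseases) from 23 tertiary rheumatology centers in 97 Brazilian cities". Participants per city, the symptomatic proportion and its variation between cities are not reported.

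**The concern.** A plain Pearson test treats each municipal proportion as an equally precise observation. A proportion based on 5 people has 500/5 = 100 times the binomial variance of one based on 500, yet both count the same.

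Two effects follow.

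- Sampling noise in the proportions enters the denominator of r but not the covariance, so r understates the correlation between local incidence and the underlying symptom risk. This happens even with equal city sizes. A regression slope or odds ratio is not diluted in this way, because the noise sits in the outcome.
- When sizes are unequal, equal weighting lets the noisiest cities dominate and loses power against an analysis that respects the denominators.

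At stake is the reading of this one analysis. A modest or non-significant r could be taken to mean that participants' symptoms do not follow the local epidemic, when part of the weakness comes from the method.

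**Working it through.** **The plan's own figure.** There is none to reproduce: no expected correlation, power or sample size is given for this analysis.

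**Inputs from the documents.** 97 cities, 10,443 participants, 5166 of them patients, hence 10,443 − 5166 = 5277 controls; 23 centers; alpha 0.05, taken as two-sided. Mean per city: 10,443/97 = 107.7. If the groups are correlated separately, the means are 5166/97 = 53.3 and 5277/97 = 54.4.

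**Inputs that must be assumed.** Symptomatic proportion p, between-city SD of the true proportion τ, true correlation ρ, and the spread of city sizes n_i.

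**Attenuation formula.** Expected r ≈ ρ × √[τ² / (τ² + E{p(1−p)} × mean(1/n_i))].

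**Equal city sizes, assumption set A.** p = 0.15; log-odds rise 0.15 per SD of log incidence; residual city SD 0.20 on the logit scale.

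- Total logit SD = √(0.15² + 0.20²) = 0.25, so ρ ≈ 0.15/0.25 = 0.60.
- τ ≈ 0.15 × 0.85 × 0.25 = 0.032; τ² = 0.00102.
- Sampling variance with 108 per city: 0.1275/108 = 0.00118.
- Factor: √[0.00102/(0.00102 + 0.00118)] = 0.68. A true 0.60 becomes about 0.41.
- One group alone, 54 per city: 0.1275/54 = 0.00236; factor √[0.00102/0.00338] = 0.55; r about 0.33.

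**Unequal sizes, set A.** Simulation with 300 runs per row, log-normal city sizes scaled to 10,443, both groups pooled. The comparator is a binomial random-intercept model on the same counts and the same covariate. Simulated true r is about 0.59.

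| Spread of city sizes (SD of log size) | Mean Pearson r | Power, Pearson | Power, mixed model |
|---|---|---|---|
| equal | 0.41 | 99% | 99% |
| 1.0 | 0.30 | 84% | 98% |
| 1.5 | 0.20 | 48% | 91% |
| 2.0 | 0.15 | 34% | 82% |

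Repeating this with precision weights in place of the mixed model gives much the same: Pearson 84%, 50% and 29% against 96%, 89% and 81% at log-SD 1.0, 1.5 and 2.0. The largest gap is 81 − 29 = 52 points.

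**Assumption set B.** p = 0.20, τ = 0.05, true r about 0.30, 4000 runs. The comparator weights each city by 1/(τ² + p(1−p)/n_i).

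| City sizes | Pearson r / power | Weighted r / power |
|---|---|---|
| all 108 | 0.24 / 66% | 0.24 / 66% |
| 14 to 510 | 0.21 / 56% | 0.22 / 59% |
| 2 to 1167 | 0.16 / 36% | 0.20 / 53% |
| 2 to 2397 | 0.10 / 18% | 0.17 / 40% |
| 23 cities hold 90% | 0.14 / 29% | 0.18 / 41% |

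Over p = 0.10 to 0.20 and τ = 0.03 to 0.08, the attenuation factor is 0.62 to 0.94 with equal sizes and 0.21 to 0.91 with unequal sizes. Weighting at true r about 0.3 gains from under 1 to about 23 power points.

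**Larger between-city variation.** Doubling both logit terms in set A (0.3 and 0.4, same true r) gives Pearson power of 99.6%, about 92% and 72% at log-SD 1.0, 1.5 and 2.0. The possible loss is then at most 0.4, 8 and 28 points.

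**Type I error.** With no true association, plain Pearson rejected in 4.3% to 5.6% of runs under the set B design. Weighting by raw participant number with the usual t test rejected in 8% to 40% when sizes were unequal.

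**The case against.** The strongest reply is that this is an efficiency refinement to a side analysis whose false-positive rate is intact. The correlation appears in neither the Objectives nor the Outcomes, and it sits next to the map plotting. A condensed article may also leave weights or a minimum city size to a fuller document, so equal weighting is inferred from a plain Pearson test with none mentioned. The side-analysis argument stands and sets the priority. The silence argument stands only in part, because the article does name the test, and the attenuation at about 108 per city does not depend on unequal sizes.

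Unequal sizes are themselves an inference. If each center lies in one city, at least 97 − 23 = 74 cities have no center, but the article does not say so and gives no city counts.

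Three stronger readings are tempting and are not supported.

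- **That the comparability of the groups rests on this correlation.** Data Collection (text after Figure 3) speaks of approaches to give patients and controls a similar path, "such as the same pandemic COVID-19 curve in each city and region", and goes on to two follow-up strategies. It never refers to the correlation.
- **That a lower r in one group could be an artefact of its city sizes.** Control Group draws controls from patients' homes and workplaces, and the totals are close (5166 and 5277). City sizes should therefore be similar in both groups. With identical sizes, the simulated mean difference in r was about 0.
- **That the test would miss a close relationship.** Power is 99% with equal sizes and 84% at log-SD 1.0 in set A. It falls badly only with strongly unequal sizes and small between-city variation, both assumed.

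A fair criticism of the comparison also stands: the simulations drew people independently within cities. Household and work contacts are likely to share symptoms, so a model with only a municipality intercept is untested under this design.

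**Conclusion.** The point holds as a minor one. Equal treatment of the municipal proportions is a poor choice for binomial data: r is biased toward zero whenever the true correlation is not zero, and power is lost when city sizes differ. The documents cannot fix the size. Under assumed inputs the power loss runs from almost none (equal sizes, or large between-city variation with moderate inequality) to about 50 points (strongly unequal sizes, small variation). If there is no true association, there is no bias and the type I error is near 5%. Nothing here bears on the patient-control comparison.

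**What to change.** In Statistical Analysis, replace the Pearson test on municipal proportions with a logistic (binomial) mixed model of symptomatic yes/no. Include log municipal incidence, group, the group-by-incidence term and a random intercept for municipality. Allow for clustering within households or contact sets, by a nested random intercept or robust standard errors. Report the odds ratio per doubling of incidence in each group, and the interaction. This also follows the section's own preference for logistic regression with dichotomous outcomes.

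If a correlation is kept for the map, label it descriptive and give no P value. Do not test it with raw participant-number weights, given the 8% to 40% type I error above.

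The cost is a short change to the text, slightly more analysis work and an effect measure less familiar than r. No new participants are needed. The article says analysis has not begun, so the change can still be prespecified.
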